## Abstract

**Background:**

New York City (NYC) is currently home to the largest Bangladeshi population in the United States (US) at approximately 62,000 individuals. The high prevalence of Type 2 diabetes mellitus (T2DM) among Bangladeshis has been well documented in Bangladesh, as well as in Canada and the United Kingdom (UK). However, little is known about the diabetes prevalence and management practices of US Bangladeshis. This paper describes the protocol for a Community Health Worker (CHW) intervention to improve diabetic management and control among Bangladeshis with diabetes in NYC.

**Methods/Design:**

For a two-arm, randomized controlled trial (RCT), investigators will recruit a sample of 256 participants, all of whom are 1) of Bangladeshi descent, 2) residing in NYC, 3) diagnosed with T2DM and a recent Hemoglobin A1c (HbA1c) of ≥ 6.5, and 4) between the ages of 21–85. The treatment group receives a six-month CHW-led intervention consisting of five monthly group educational sessions, two one-on-one visits, and follow-up phone calls as needed from a CHW. The control group receives an introductory educational session only. Primary and secondary outcomes include clinical and behavioral measures, such as HbA1c and weight change, access to and utilization of care (i.e. appointment keeping and use of specialty care), and knowledge and practice of physical activity and healthful eating. Additionally, information regarding CHW characteristics, the processes and mechanisms for influencing healthful behavior change, and fidelity of the intervention are collected. Outcomes are measured at Baseline, 3-Months, 6-Months for both groups, and at 12-Months for the treatment group.

**Discussion:**

To our knowledge, this study represents the first attempt to document the efficacy of T2DM management strategies in the NYC Bangladeshi population. Thus, future qualitative and quantitative findings of the submitted protocol will fill an important gap in the health disparities literature.

**Trial registration:**

NCT02041598

## Background

New York City (NYC) is currently home to the largest Bangladeshi population in the United States (US). From 2000 to 2010, the Bangladeshi population in NYC experienced a 119% increase in size, growing from 28,269 to 61,788 individuals [1]. In contrast, the Asian American community in NYC overall increased by 30%. The addition of approximately 33,000 Bangladeshis to the city’s diverse cultural landscape represented the second-largest numerical increase among Asian groups in the city in the last decade. World Health Organization (WHO) estimates placed Bangladesh on the top ten list of countries with the highest number of estimated cases of Type 2 diabetes mellitus (T2DM) prevalence in 2000 [2]. WHO projections for 2030 estimate the prevalence of T2DM in Bangladesh to increase to over 11 million. Although the prevalence of T2DM among Bangladeshis has been well documented in the home country [2-5], as well as in Canada and the U.K [6,7], little is known about its prevalence and management practices among US Bangladeshis. Studies conducted among South Asian populations (which include individuals from India, Pakistan, and Bangladesh) in the US have found that these groups are 4 to 7 times more likely to suffer from T2DM than the general population [8-10]. Several community-based samples of Bangladeshis in NYC report diabetes prevalence rates in the range of 17-25%, as compared to 10% in non-Hispanic whites [10-12].

In addition to being disproportionally at risk for diabetes, Bangladeshis in NYC have a unique demographic profile that may impact access to and utilization of care, resulting in poorer health outcomes. According to the US Census, 53% of Bangladeshis in NYC speak English less than “very well” and approximately 33% live below the poverty line (compared to the citywide average of 19%) [1]. The above demographic factors, coupled with an increased risk profile for diabetes, highlight the need for culturally- and linguistically-relevant interventions in this community. Community Health Workers (CHWs) have been suggested as a culturally-based strategy to address this need among other ethnic and immigrant populations. CHWs are generally indigenous to the community in which they work -- ethnically, linguistically, socioeconomically, and experientially – providing them with a unique understanding of the norms, attitudes, values, and strengths of community members [13,14]. This understanding is incredibly valuable given the growth of minority and underserved populations whom health care providers have difficulty reaching or communicating with [15,16]. Moreover, given that the nature of chronic disease requires long-term management and life-style modification, the use of CHWs is increasingly being viewed as a low-cost approach to improving community health and well-being, reducing health disparities, and bridging the cultural and social barriers between underserved communities and the health care system [14,17].

While there has been formative work to study the role of health beliefs, behaviors, and barriers to/facilitators of T2DM management in this community [18,19], no known studies to date have tested the efficacy of a CHW intervention in the Bangladeshi community. We present the protocol of a research study designed to fill this gap in knowledge. The DREAM (Diabetes Research, Action, and Education for Minorities) Project is a 6-month randomized controlled trial (RCT) that utilizes the CHW model to improve diabetic control and management among Bangladeshis living in NYC.

## Methods/Design

### Objectives

The primary aim of the current study is to assess the efficacy of a CHW intervention to improve management and control among Bangladeshis with T2DM in NYC. Secondary aims include examining the intervention’s effect on diabetes knowledge, self-management practices, health behaviors, and access to primary and specialty care services among study participants.

### Ethics approval

The study protocol and procedures were approved by the Institutional Review Board at the New York University School of Medicine on July 6, 2009. Written informed consent is obtained from study participants by trained CHWs or study personnel prior to enrollment.

### Sample size calculations

The size of the study population is based on the primary outcome measure of HbA1c and was estimated by using previous changes observed in a pilot study as well as in previous research [19,20]. Control group HbA1c estimates were based on hospital patients receiving usual care. An absolute difference of 0.5% in HbA1c between the groups (6.7 vs. 6.2) with a power of 0.8 and significance level of 0.05 may be detected with a total of 40 individuals in each group, and an absolute difference of 0.3% in HbA1c between the groups (6.7 vs. 6.4) with a power of 0.8 and significance level of 0.05 may be detected with a total of 120 individuals in each group. The sample size calculation was based on a medium effect size of the primary outcomes between the intervention and control group. Approximately 256 enrolled study participants were randomized each to the treatment and control groups. We anticipated that 75% of study participants would be followed to completion of the study at 6 months (n = 96 in each group).

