### Study participants

The study population of interest is Bangladeshi individuals residing in NYC that have been diagnosed with T2DM. Study eligibility includes the following:

(a) confirmed clinical diagnosis of T2DM with a Hemoglobin A1c (HbA1c) of ≥ 6.5%; *and*

(b)  male or female between the ages of 21–85 years old; *and*

(c) willingness to be randomized to either treatment or control groups.

Participants are ineligible for enrollment in the study if s/he:

(a) is or was on renal dialysis; *or*

(b)  is experiencing an acute or terminal illness or serious mental illness; *or*

(c)  had a history of recent coronary event within the last 3 months of recruitment; *or*

(d)  is pregnant at the time of recruitment; *or*

(e)  experienced other severe medical conditions that might preclude participation; *or*

(f) has poor short-term prognosis (expected death in <2 years); *or*

(g)  is participating in another research study.

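### The power calculation uses a control mean HbA1c of 6.7 with an implied SD near 0.8. This does not fit a trial that admits only people at 6.5% or above, and the planned 96 completers per arm fall short of the 120 stated for a 0.3% difference.

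*Protocol article*

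**What the plan says.** All the inputs are in the protocol article.

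- **Sample size calculations, scenario 1:** "An absolute difference of 0.5% in HbA1c between the groups (6.7 vs. 6.2"), which the text says "with a power of 0.8 and significance level of 0.05 may be detected with a total of 40 individuals in each group".
- **Sample size calculations, scenario 2:** "an absolute difference of 0.3% in HbA1c between the groups (6.7 vs. 6.4"), which the text says "with a power of 0.8 and significance level of 0.05 may be detected with a total of 120 individuals in each group".
- **Source of the inputs:** the size "was estimated by using previous changes observed in a pilot study as well as in previous research", and "Control group HbA1c estimates were based on hospital patients receiving usual care". No SD is printed, nor whether the test is one- or two-sided.
- **Planned numbers:** 256 enrolled and 75% followed to 6 months, giving 96 per group. Since 0.75 × 128 = 96, this means 128 randomised per arm.
- **Study participants:** entry requires a "confirmed clinical diagnosis of T2DM with a Hemoglobin A1c (HbA1c) of" at least 6.5%. The Abstract gives the same floor and asks for a recent value.
- **CHW intervention:** controls receive one introductory session and otherwise continue with their usual medical care.

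**The concern.** Everyone enters at 6.5% or above, so the baseline mean must lie above 6.5 by an amount that depends on the spread. Controls then receive little beyond usual care, and the article gives no reason to expect their mean to fall. A control mean only 0.2 above the floor, combined with an SD near 0.8, looks like a description of a population that includes many people the trial would not admit. The article does not say whether the hospital or pilot patients met the floor.

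The SD is what is at stake. It drives both 40 and 120 per group, it is not printed, and it appears to come from a population other than the eligible one. A second question follows from the article's own numbers: how much power do 96 completers per arm give for the smaller of the two differences? If the answer is well below 80%, a null result could be over-read as evidence against a 0.3% effect.

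**Working it through.** **Step 1. Recover the SD from the printed sample sizes.** For two means, n per group = 2·SD²·(z₀.₉₇₅ + z₀.₈₀)²/δ², with z₀.₉₇₅ + z₀.₈₀ = 1.960 + 0.842 = 2.802 (two-sided test assumed). Rearranged, SD = δ·√(n/2)/2.802.

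- n = 40, δ = 0.5: 0.5 × √20 / 2.802 = 0.798 (t-test version 0.788).
- n = 120, δ = 0.3: 0.3 × √60 / 2.802 = 0.829 (t-test version 0.826).

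A single SD of 0.817 returns 42 and 117 per group, so the two printed figures agree with each other to within rounding. A one-sided test would imply 0.90 and 0.94 by the same formula.

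**Step 2. Compare with the entry floor.** For a normal distribution with mean 6.7 and SD 0.80, the share below 6.5 is Φ((6.5 − 6.7)/0.80) = Φ(−0.25) = 0.40. With SD 0.83 it is also 0.40. Keeping only the part at or above 6.5 gives mean 7.22 and SD 0.52 (7.24 and 0.54 for SD 0.83).

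To hold both a mean of 6.7 and an SD of 0.8 above a floor of 6.5, the shape must be extreme. A gamma distribution starting at 6.5 would need about 72% of people within 0.01 of the floor. More ordinary shapes with SD 0.8 above that floor have means of about 7.3 (shifted exponential) or 7.6 (half-normal).

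**Step 3. Power with 96 completers per arm.** Power = Φ(δ/(SD·√(2/96)) − 1.960), and detectable difference at 80% power = 2.802·SD·√(2/96). The SDs below 0.79 and above 0.83 are assumptions, because the article gives none.

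| SD | Power, 0.3% | Power, 0.5% | Detectable difference |
|---|---|---|---|
| 0.52 (truncated normal, step 2) | 98% | >99% | 0.21 |
| 0.70 | 84% | >99% | 0.28 |
| 0.79 | 75% | 99% | 0.32 |
| 0.80 | 74% | 99% | 0.32 |
| 0.83 | 71% | 99% | 0.34 |
| 1.0 | 55% | 93% | 0.40 |
| 1.2 | 41% | 82% | 0.49 |
| 1.5 | 28% | 64% | 0.61 |

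The t-test gives values within about one percentage point (70% at SD 0.83).

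**Step 4. Break-even SDs at 96 per arm.** For 80% power the SD may be at most δ·√48/2.802. For 0.3% this is 0.74. For 0.5% it is 1.24 (1.23 by the t-test).

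**The case against.** **The means do not enter the formula.** This stands. Only the difference and the SD matter, so removing 6.7, 6.2 and 6.4 would leave 40 and 120 unchanged. The two figures agree with each other, and no arithmetic error is shown. The 6.7 matters only as evidence that the inputs describe a different population.

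**The floor applies at entry, while 6.7 may be a 6-month mean.** This stands in part. Regression to the mean could carry some controls below 6.5, but the article does not argue this and gives usual-care hospital patients as the source. For the treated arm the objection succeeds fully. A reader might take means of 6.2 and 6.4 as contradicting the criterion, but a follow-up mean below the entry threshold would be the intended effect.

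**The eligible group need not be more variable.** This stands. A reader might infer that the trial is badly underpowered for the whole 0.3–0.5% range. The documents do not support that. Truncation alone narrows the baseline spread, and at SD 0.52 power for 0.3% would be 98%. A wider eligible population would lower power. Nothing in the article settles which applies.

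**An SD near 0.8 could be an SD of change.** This is possible, since the text mentions earlier changes. However, the differences are written as group levels, and the Data analyses section plans t-tests without naming change scores. If change was meant, the section needs correcting on that point instead.

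**An article may leave the SD to the full protocol.** This is fair for the missing SD alone. It does not cover a printed control mean that sits badly with the printed eligibility rule, or 96 completers set beside a stated need for 120.

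**Conclusion.** The point holds in a limited form, with two separate parts.

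1. **Unsupported SD.** The implied SD of about 0.79–0.83, paired with a usual-care control mean of 6.7, does not plausibly describe people admitted at 6.5% or above. The article does not reconcile the two. The SD behind 40 and 120 per group is therefore unsupported for the eligible population. It is not shown to be wrong, and the direction of any error is unknown. This rests on a two-sided test and, for the 40% figure, on a normal shape.

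2. **Shortfall for 0.3%.** This part does not depend on the floor. At an SD of 0.80–0.83, 96 completers per arm give about 70–74% power for 0.3% (75% at 0.79), with a detectable difference of about 0.32–0.34%. The 80% is stated for 120 per group, more than the plan expects to complete. The article does not claim 80% at 96 in so many words, but it gives both numbers together without saying that the smaller difference is no longer covered at that power.

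The larger difference is well protected. Power for 0.5% is about 99% at the implied SD and stays at or above 80% up to an SD of about 1.23.

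**What to change.** In the sample size section:

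- State the SD, its source, the sidedness of the test, and whether the source patients met the 6.5% floor.
- Replace that SD with the pooled baseline SD of participants enrolled since February 2011, computed without reference to arm. All of them were at or above 6.5%.
- Restate power as the 6-month difference detectable with 96 per arm, over SDs both below and above 0.8 and over a range of baseline–follow-up correlations. The range is needed because the floor acts at baseline only, so follow-up values may be more spread out.
- Withdraw the 80% power claim for 0.3% unless the new SD supports it. Without baseline adjustment, that needs an SD of no more than about 0.74.

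If the analysis adjusts for baseline HbA1c, the detectable difference is multiplied by √(1 − ρ²). With an assumed ρ of 0.5, for example, SD 0.8 gives 0.323 × 0.866 = 0.28 and SD 1.2 gives 0.485 × 0.866 = 0.42. The power statement should use this only if the analysis section commits to that adjustment.

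The cost is one blinded SD calculation and revised text. No extra patients are needed, and allocation is not used. The stated figure may become less favourable.

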### Study participants

The study population of interest is Bangladeshi individuals residing in NYC that have been diagnosed with T2DM. Study eligibility includes the following:

(a) confirmed clinical diagnosis of T2DM with a Hemoglobin A1c (HbA1c) of ≥ 6.5%; *and*

(b)  male or female between the ages of 21–85 years old; *and*

(c) willingness to be randomized to either treatment or control groups.

Participants are ineligible for enrollment in the study if s/he:

(a) is or was on renal dialysis; *or*

(b)  is experiencing an acute or terminal illness or serious mental illness; *or*

(c)  had a history of recent coronary event within the last 3 months of recruitment; *or*

(d)  is pregnant at the time of recruitment; *or*

(e)  experienced other severe medical conditions that might preclude participation; *or*

(f) has poor short-term prognosis (expected death in <2 years); *or*

(g)  is participating in another research study.

### Study design

Aggregated patient registry data from a large, public hospital in NYC was used to gauge the approximate size of the community served at this particular healthcare institution. A targeted enrollment of n = 256 was used for this study as previously described in the power calculation. The projected sample size also takes into account previous literature detailing refusal and attrition rates for peer- and CHW-led health interventions [21-23].

The study is a two-arm RCT design. Following screening, consenting, and study enrollment, participants are randomly assigned to either treatment or control group by a blinded study staff member using IBM SPSS Statistics, Version 19.0 (IBM Corp). Study groups are stratified by gender and age. Both study staff and participants are notified of subject randomization allocation. Additionally, all participants randomized to the control groups are offered the opportunity to receive the full intervention after serving as a control for the 6-month study period. This strategy is part of a multi-pronged effort to improve data collection rates among participants randomized to the control group, as well as an effort to conduct the study in alignment with the principles of community-based participatory research (CBPR) and in response to community concerns regarding the ethics of withholding potentially beneficial interventions for community members.

### Study recruitment

We drew upon literature which suggested that a multi-pronged recruitment approach that considers cultural and contextual factors impacting participation in research should be applied [24-27]. One strategy employed includes the use of a mass mailing and phone-follow-up to potential participants recruited from a public hospital in NYC that serves a large Bangladeshi patient population. Patients are sent introductory letters describing the study and providing promotional materials, both of which were in Bengali and English. Patients then receive a follow-up phone call from a CHW approximately two weeks later, at which time additional study information is provided and eligibility information is obtained via a standardized script and screening questionnaire. The screening tool includes questions related to the protocol-specified inclusion/exclusion criteria, as well as questions regarding planned travel to the home country, which was identified as a significant barrier to retention during the formative phase of this study [18]. The above recruitment protocol has also been previously used in several diabetes and lifestyle interventions primarily targeting Caucasian and Hispanic participants [28,29]. Figure 1 illustrates the flow of recruitment and enrollment using this approach.

**Figure 1 F1:**
[figure not shown]
Recruitment process flowchart (Mass Mailing).

In addition to the mailing and phone follow-up, screening and tabling events are also held in the hospital atrium 2–3 times per week during the recruitment periods. CHWs provide study recruitment materials in Bengali to interested study participants who are passing to and from clinic appointments, and screen those interested in participation. During these encounters with potential participants, contact information is also obtained, so that CHWs can complete additional follow-up and continue to build rapport with interested participants prior to obtaining informed consent for participation in the intervention. Figure 2 illustrates the flow of recruitment and enrollment using this approach.

**Figure 2 F2:**
[figure not shown]
Recruitment process flowchart (Recruitment/Tabling Event).

Other recruitment methods employed include “snowball” or word-of-mouth referrals, which are accepted from screened and enrolled participants. The project staff also works with local faith-based and community-based organizations to do outreach and screening events in neighborhoods in close proximity to the hospital site. Lastly, articles are placed in local Bangladeshi newspapers which include information regarding the study and (in some cases) contact information for study staff. These articles are published with the intention of promoting general awareness of the program among the community of interest, and not as a direct recruitment tool.

### CHW intervention

Individuals randomized to the treatment group receive a multi-component intervention comprising of group educational sessions, one-on-one visits, and phone follow-up by one of three full-time CHWs. Group educational sessions occur once per month, for five months, and are held in a community-based or hospital setting. Each session is conducted in Bengali and involves a discussion of different content areas related to T2DM, such as nutrition, physical activity, and complications of diabetes. Educational sessions are guided by the Health Belief Model [30] and Social Support Theory [31]. For example, in describing diabetes, CHWs explain the prevalence of T2DM and described risk factors. These discussions are intended to make participants aware of their risk and to enhance participants’ acceptance of their diabetes diagnosis—i.e., altering participants’ perceived susceptibility to diabetes. Educational sessions are also supplemented with materials/handouts that have been adapted from standardized curriculums and translated for use in the Bangladeshi community [19]. Materials are tailored with specific cultural and religious practices in mind, with guidance and input from both project CHWs and a community coalition comprised of representatives from academic institutions, healthcare agencies, and community-based organizations [32]. Project staff and coalition also utilize results from a mixed-methods formative research study that were completed prior to study implementation with the target community to help guide the process of tailoring materials and curriculum content [18].

In addition to educational sessions, treatment group participants receive two one-on-one visits during the six month study period. Each visit provides study participants with the opportunity to discuss individualized care needs related to diabetic management with a CHW, as well as to discuss goal-setting around health behaviors using motivational interviewing techniques. CHWs also help to provide referrals to specialty care (e.g. podiatry and dentistry), as well as to social service or community-based resources for needs related to housing, food assistance, immigration, etc. Lastly, CHWs utilize phone follow-up between educational sessions and one-on-one visits to both encourage adherence to discussed care plans, as well as to improve study retention and data collection rates by minimizing study drop-out. All of the above interactions with study participants are documented in CHW progress notes and call logs to ensure fidelity to study protocol as well as to capture secondary study outcomes related to access to and utilization of care.

Individuals randomized to the control group receive a one-time, introductory educational session only. This session focuses on general concepts regarding diabetes management, and is the same introductory session received by the treatment group. Individuals randomized to the control group are instructed to seek medical care as usual from their regular physician. Previous literature has underscored the importance of providing meaningful incentives as a strategy to maximize retention in community-based studies [33]. Accordingly, participants are provided round-trip MetroCards® ($4.50 - $5 value) at each educational session and at each data collection timepoint. Additionally, treatment group participants are given a small incentive related to the session topic (e.g. bag of brown rice, pill box, pedometer, etc.) at each session, as well as a ticket towards a $100 raffle drawing to be completed at the end of the intervention period.

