### Data analyses

Analyses to compare the treatment and control group participants are conducted at baseline to detect significant differences. Student t-tests for normally distributed variables (after necessary transformations) and chi-squared tests for categorical variables were used. In the event that randomization did not control for differences between the treatment and control groups on baseline characteristics, we statistically controlled for those differences in subsequent analyses of program effects. Descriptive statistics are conducted to characterize study participants and to evaluate the distribution of key exposure and outcome variables, as well as to describe the factors that affect utilization of health care services and the risk and protective factors for diabetes. Summary data on medical history, length of time in the US, access and utilization to primary health care services, and social characteristics (e.g., marital status, employment, education) is reported.

The primary goal of this study is to evaluate intervention efficacy, using the generally accepted approach in evaluating efficacy trials, Intention to Treat (ITT) [43]. The analysis for each aim will be comprised of t-tests for continuous variables and chi-square tests for categorical variables. Indexes will be created for scale variables and examined as continuous variables. Mann–Whitney U Tests will be applied for indices with non-parametric distributions.

Each aim will be tested using multivariate logistic regression analysis. The base model will consider the intervention group as the primary predictor variable. Interaction terms between treatment and follow-up time will be developed to assess whether the effect of treatment varied over time. A third set of models included other covariates identified in the preliminary analysis as potential confounders that may reduce the likelihood of confounding bias. Goodness-of-fit of the final models will be assessed using the Hosmer-Lemeshow test.

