## Discussion

To our knowledge, this study represents the first attempt to document the efficacy of diabetes management strategies in the NYC Bangladeshi population. Thus, the future qualitative and quantitative findings of the submitted protocol will fill an important gap in the health disparities literature. Additionally, this study aims to characterize the specific mechanisms through which CHWs operate to fulfill their role as a bridge between the community and the healthcare system. This information will help to provide a more concrete exploration of the specific characteristics of a CHW that may be related to their efficacy in improving health outcomes. Lastly, we anticipate that the collection and reporting of detailed process evaluation metrics related to both the study recruitment and implementation phases will help to inform the design of future CHW interventions/programs.

There are several limitations to the current study. First, blinding study staff or participants to randomization allocation is not feasible, and thus may result in ascertainment bias and subsequent threat to study validity. Additionally, since control group participants do receive an introductory session that contains general information regarding diabetes management, individuals may make subsequent behavior changes leading to positive clinical outcomes that would make observation of between-group differences problematic. However, because the study is guided by CPBR principles, investigators felt that the current study design was a reasonable tradeoff between what is scientifically rigorous and what is valuable to the community. Lastly, since many individuals reside in the same neighborhoods in NYC, there is a potential for contamination bias between the two arms to occur. Investigators will attempt to control for this through measuring interaction between study participants via the survey questionnaire.

Recruitment for the study began in February 2011, and will be conducted in phases or cohorts (rather than on an ongoing basis). Enrollment and data collection is scheduled to conclude by November 2014, at which time final data analysis will commence and study findings will be reported in a separate publication.

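### Treatment-arm participants share session groups and CHWs, but the named tests and the sample size treat them as independent; if outcomes correlate within groups, the standard error is too small

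*Protocol article*

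**What the plan says.** Under Study design, individuals are randomised, with stratification by gender and age. Under CHW intervention, the treatment arm receives "group educational sessions, one-on-one visits, and phone follow-up by one of three full-time CHWs". The group sessions run monthly for five months, and each participant also has two individual visits. Controls have a single introductory session, the same one the treatment arm gets.

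Under Data analyses: "The analysis for each aim will be comprised of t-tests for continuous variables and chi-square tests for categorical variables". Mann–Whitney tests are kept for skewed indices, and each aim is also tested by logistic regression. The model terms described are treatment, treatment by follow-up time, and confounders. No term for session group or CHW is named.

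Under Sample size calculations: "An absolute difference of 0.5% in HbA1c between the groups" (6.7 against 6.2) "with a power of 0.8 and significance level of 0.05 may be detected with a total of 40 individuals in each group". For a 0.3-point difference (6.7 against 6.4) the same section says "with a power of 0.8 and significance level of 0.05 may be detected with a total of 120 individuals in each group". Retention of 75% is expected, giving 96 per group at 6 months. No SD, ICC or design effect appears.

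The Discussion raises dependence between participants only as contamination between arms.

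**The concern.** This is an individually randomised trial with group delivery in one arm, usually called a partially nested design. People who attend the same sessions, or are supported by the same CHW, share content, peers and the skill of the person delivering it. The article itself points this way. Sessions rest partly on Social Support Theory, and the Discussion hopes to learn which CHW characteristics relate to efficacy.

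If outcomes are positively correlated within a session group, 96 treatment completers carry less information than 96 independent people. A t-test or ordinary logistic regression does not see this. Its standard error is too small, its interval too narrow and its p-value too low. The sample-size statement is optimistic for the same reason. At stake is whether the reported precision of the HbA1c effect can be trusted.

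**Working it through.** **Inputs from the article.** Significance level 0.05 (taken as two-sided); power 0.80; 40 per group for a 0.5 difference and 120 per group for 0.3; 256 enrolled, so 128 per arm; 96 completers per arm; three CHWs.

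**Inputs assumed.** ICC 0.01–0.05; session groups of 8, 12 or 15 completers; SD 0.81.

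**Step 1: the plan's own figures.** 128 × 0.75 = 96, as stated. The SD can only be back-solved: SD = difference × √(n/2) / (1.96 + 0.84).

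- n = 40, difference 0.5: SD ≈ 0.798
- n = 120, difference 0.3: SD ≈ 0.829

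The two are close but not identical. An SD of 0.81 lies between them. Both sample sizes match an ordinary independent-groups formula with an SD near 0.8, so no clustering allowance is visible.

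**Step 2: effect of clustering in one arm.** With m completers per session group:

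- Treatment-arm design effect: DE = 1 + (m − 1) × ICC
- True variance of the difference ÷ naive variance: R = (DE + 1)/2, because the control arm is not inflated
- Actual two-sided type I error of the nominal 5% test: 2 × [1 − Φ(1.96/√R)]
- Power of a test using the true standard error: Φ(0.3/(0.81 × √(2/96) × √R) − 1.96), where 0.3/(0.81 × √(2/96)) = 2.566

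With no clustering (R = 1), power is Φ(2.566 − 1.96) ≈ 73%.

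| m | ICC | DE | R | True SE ÷ naive SE | Type I error | Power for 0.3 |
|---|---|---|---|---|---|---|
| 8 | 0.01 | 1.07 | 1.035 | 1.02 | 5.4% | 71% |
| 8 | 0.05 | 1.35 | 1.175 | 1.08 | 7.1% | 66% |
| 12 | 0.01 | 1.11 | 1.055 | 1.03 | 5.6% | 70% |
| 12 | 0.05 | 1.55 | 1.275 | 1.13 | 8.3% | 62% |
| 15 | 0.01 | 1.14 | 1.070 | 1.03 | 5.8% | 70% |
| 15 | 0.05 | 1.70 | 1.350 | 1.16 | 9.2% | 60% |

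**Step 3: check by simulation.** A naive t-test with 8 treatment groups of 12 and 96 independent controls (20,000 runs per setting) rejected in 5.6%, 6.4% and 8.3% of runs at ICC 0.01, 0.02 and 0.05. The formula gives 5.6%, 6.3% and 8.3%.

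**Step 4: recruitment cohorts.** With four cohorts shared equally by both arms and no other clustering, the naive t-test rejected in 4.1–4.6% of runs, so there was no inflation.

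**The case against.** The strongest case against is that this is a condensed article and a fuller plan could add a cluster term. That limits the point to the methods named here. It does not remove it, because the article names the tests for every aim and gives a sample size, and neither allows for clustering.

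Second, the size is conditional. With an ICC of zero there is no problem, and at ICC 0.01 with groups of 8 the type I error is 5.4%, which is trivial. This stands. A reader might infer that false positives will exceed 5%; the article cannot support that. If the intervention affected nobody, individual randomisation would keep the test near 5%. Inflation needs group or CHW effects that vary around a zero average. The narrow intervals do not need a zero average, only effects that vary by group or CHW.

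Third, a reader might apply the formula to the CHWs. With 96/3 = 32 completers each it gives 6.8–14.1% for ICC 0.01–0.05. That treats three CHWs as random draws from a larger population, and three are too few to estimate such a variance. For inference about these three CHWs the design effect does not apply, so these figures are not the size of the problem.

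Fourth, recruitment "will be conducted in phases or cohorts (rather than on an ongoing basis") may look like another layer of clustering. These are enrolment phases, and nothing suggests that they differ by arm. Step 4 shows no inflation, so cohorts are not part of the defect.

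Finally, the article does not say that session groups are closed or that a participant keeps one CHW throughout. This stands, and the fix must allow for it.

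**Conclusion.** The point holds in conditional form. Delivery is grouped in one arm only, and the analyses and sample size in the article take no account of it. If within-group correlation is positive, the standard error is understated, by a factor of about 1.02 to 1.16 over the assumed range (ICC 0.01–0.05, groups of 8–15, 96 completers per arm). Where group or CHW effects vary around a zero average, the nominal 5% test then has a type I error of about 5.4–9.2%. With SD 0.81, power for a 0.3-point difference falls from about 73% to about 60–71%. The ICC, the group size and the SD are all assumptions.

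The shortfall from the planned 80% to about 73% is a separate matter. It comes from having 96 completers where the article's own figure is 120, and should not be charged to clustering. Only the further loss of about 2 to 13 points belongs here.

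**What to change.** - **Record the clustering.** Take each treatment participant's usual session group and CHW from the contact notes and call records that CHWs already keep.
- **Continuous outcomes.** Use a partially nested linear mixed model: random intercept for session group in the treatment arm only (controls as singletons), residual variance specific to arm, and Satterthwaite or Kenward–Roger degrees of freedom.
- **Binary outcomes.** Use the logistic mixed counterpart, or GEE with a small-sample correction.
- **Movement between sessions.** Assign participants to the group they attended most, or use a multiple-membership model.
- **CHW.** Report CHW as a fixed factor in a sensitivity analysis.
- **Sample size section.** State the assumed SD and restate the detectable difference at 96 completers per arm over an ICC range.

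No extra participants or visits are needed. Final analysis is scheduled after data collection ends, so the wording can still change. The cost is slightly wider intervals and a less favourable power figure.
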